### Recruitment, screening, and consent

2.5

The research team will work with the BDI marketing and communications team to recruit participants by providing advertisements on social media (i.e. Facebook, Instagram) and emailing health professionals on an internal BDI mailing list of health professionals interested in research participation.

Additionally, independent industry organisations Barwon Health, Peninsula Health, Royal Melbourne Hospital, and La Trobe Regional Hospital will be invited to distribute study advertisements to their medical employee networks. Potential participants will be provided with a REDCap link to the Patient Information Statement and Consent Form (PISCF) where they can view more information about the trial. The contact details for the Coordinating Principal Investigator will be provided in recruitment materials and the PISCF to offer potential participants the opportunity to ask questions and seek further information.

Following consent, an online screening survey will be completed through REDCap. It will ask potential participants to confirm the inclusion criteria, as well as complete a modified version of the DASS-21 to confirm the absence of exclusion criteria. The modified DASS-21 includes two risk-related items addressing suicidal ideation (“I had thoughts that I would be better off dead, or thoughts of hurting myself in some way”) and problematic use of alcohol or drugs (“I found it difficult to control my consumption of alcohol or other drugs”) rated on the same 0–3 scale as the other questions in the DASS-21 ranging from “Did not apply to me at all” to “Applied to me very much or most of the time”. Potential participants are ineligible to participate if they report DASS-21 symptom scores in the Severe or Extremely Severe ranges for anxiety (DASS-21 anxiety subscale score >7) or depression (DASS-21 depression subscale score >10) or report suicidal ideation or problematic alcohol or drug use (score >1 on respective questions). If a person does not meet the inclusion criteria, they will be notified by a message within the online survey. Branching logic will be used to present the participant with the relevant reason(s) that they were not eligible and, where relevant, provide links to crisis services and/or TEN where they may find support. If a person reports suicidal ideation or problematic alcohol or drug use during screening (rating of “Often” or “Almost Always” on screening items addressing these criteria) a clinical psychologist (PB or MB) will contact the participant directly by email to direct the person to appropriate supports.

To confirm that all participants are registered doctors following successful online screening and prior to data collection, potential participants' name, postcode, and profession will be checked against the Australian Health Practitioner Regulation Agency (AHPRA) database – a publicly available list of registered health professionals in Australia. In the event that a participant's registration cannot be verified, they will be contacted by email for clarification.

### Randomisation

2.6

Eligible participants will be randomly allocated to the blended care, self-guided, or active attention control arm using a 1:1:1 ratio. Randomisation will be completed following completion of baseline outcomes.

A randomisation list in a Microsoft Excel file will be prepared in advance using a random number generator using block sizes of 6, 9, and 12. When a participant is ready to be randomised, the list holder will be contacted, and the allocation provided. Participants will be informed which treatment they have been randomly assigned via email.

### Blinding

2.7

By nature of the interventions being examined, complete single blinding of participants to intervention allocation is not possible. Instead, to improve allocation concealment participants will be informed that the trial is examining a bespoke burnout intervention for health professionals containing both person-to-person and self-guided digital components and that they may be allocated to receive one or all these components. This procedure will serve to ensure that allocation concealment between the self-guided Navigating Burnout and active attention control is maintained.

As Navigating Burnout is currently publicly available through TEN without registration, there is a risk that participants in the active control arm could access Navigating Burnout outside the scope of the trial. As such, references to TEN and Navigating Burnout will be limited in recruitment materials and the PISCF to reduce the risk of contamination.

### Procedure

2.8

Eligible participants will complete baseline surveys (demographics and psychometrics) before random allocation to self-guided, blended, or active attention control. All arms will access their allocated treatment over 10 weeks. Participants will complete follow-up surveys (psychometrics, service acceptability questions) immediately post-treatment, and again three months post-treatment to assess maintenance of therapeutic effects.

Following completion of the 3 months post-treatment survey, or once participants are considered lost to follow-up at the 3 months post-treatment timepoint, participants allocated to the self-guided or active attention control will be provided with information about TEN, including information on how to access the self-guided Navigating Burnout and/or person-to-person care.

Participants will complete 6 psychometric questionnaires: Oldenburg Burnout Inventory (OLBI; burnout) [22], Depression Anxiety Stress Scale (DASS-21; depression and anxiety) [23], Work and Social Adjustment Scale (WSAS; psychosocial functioning) [24], World Health Organisation Health and Work Performance Questionnaire (WHO-HPQ; workforce participation) [25], Turnover Intention Scale-6 (TIS-6; workforce attrition) [26], and Client Satisfaction Questionnaire (CSQ-8; intervention acceptability) [27]. To further assess acceptability, bespoke questions regarding the self-reported usage and acceptability of Navigating Burnout will also be employed, alongside open-ended questions about participants’ experiences with their allocated treatment and their experiences of burnout.

The OLBI, DASS-21, WSAS, WHO-HPQ, and TIS-6 will be completed at baseline, post-treatment, and 3 months post-treatment, while the CSQ-8 and service acceptability questions will only be completed at the post-treatment timepoint. See Table 1 for an overview of measures employed across trial timepoints. Regular safety audits (2–3 times per week) of the post-treatment and 3 months post-treatment surveys will be conducted, and any responses indicative of distress or suicidal ideation will be reported to PB. If a participant consented to a check-in call related to indicators of distress or suicidal ideation, a clinical psychologist (PB or MB) will contact the participant immediately.

**Table 1 tbl1:** Measures employed across trial timepoints.

Measure	Baseline	Post-treatment	3 months post-treatment

Demographics	X		
OLBI	X	X	X
DASS-21	X	X	X
WSAS	X	X	X
WHO-HPQ	X	X	X
*TIS-6*	X	X	X
CSQ-8		X	
Self-reported service usage		X	X
Objective service usage		X	X
Open-ended service acceptability		X	
Open-ended burnout	X	X	X

In the blended care arm, participants will be asked to complete an additional OLBI and DASS-21 if their first consultation is arranged for more than three weeks after their baseline survey is completed. This measure will be provided to participants two weeks before their first consultation date. This will ensure the primary outcome remains valid despite delays to treatment start in the blended care arm (e.g., due to treating clinicians being at capacity or participants' availability), as well as provide treating clinicians with updated data on participants’ current mental health.

To aide participant retention, participants will be reimbursed for their participation by means of a $25 digital gift card sent via the GiftPay system to their nominated email at the completion of each measurement point (i.e. baseline, post-treatment, and 3 months post-treatment). To minimise attrition, participants who do not return survey data will receive up to 3 automated survey reminders via email every 2 days from the initial survey invitation date. Those who do not return survey data after 2 weeks past the final automated reminder will receive a final reminder from a member of the research team sent from the trial email account. To further aide engagement in the in the blended care arm, participants will liaise with a member of the research team or patient care coordinator from the Black Dog Institute Clinical Service regarding consultations and attendance (e.g. organising of consultations in a piecemeal manner when a participant cannot commit to all 5 sessions from initial contact due to scheduling issues, rescheduling of cancelled appointments, etc).

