### Participants

2.2

Individuals will be eligible to participate in the trial if they satisfy all of the following criteria.•registered doctor currently practising in Australia;•able to read and speak English fluently;•current experience of self-reported burnout;•able to access the internet in a private location on a device suitable for viewing websites and attending telehealth consultations; and•able to attend telehealth consultations during Monday to Friday business hours (9.00–17.00).

Individuals will be excluded from trial participation if they satisfy any one or more of the following criteria.•current diagnosis of severe mental illness that requires more specialist support (e.g., bipolar disorder, schizophrenia, etc.);•current engagement with person-to-person psychological therapy (e.g. cognitive-behavioural therapy);•DASS-21 symptom scores in the Severe or Extremely Severe ranges for anxiety or depression during screening; or•report suicidal ideation or problematic alcohol or drug use during screening.

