**Fig. 2 fig2:**
[figure not shown]
Example screenshot from Navigating Burnout.

In the blended care arm, a clinical psychologist from the BDI Clinical Service will work through the Navigating Burnout content with participants over 10 weeks in five fortnightly 1-hour consultations. Clinical psychologists will follow a treatment manual mirroring the content of Navigating Burnout, with guidance on integrating digital content into session activities. Session 1 covers understanding burnout and self-care, session 2 covers unrealistic expectations, session 3 covers setting limits, session 4 covers valued living, and session 5 covers increasing social connections and information for managers. Session 1 is fixed and the same for all participants, whereas sessions 2–5 occur in an order determined by the participant and their clinical psychologist. Clinical psychologists will be offered a training program comprising [1]: a comprehensive treatment manual summarising the study protocol, the digital content, and session plans with suggested approaches to delivering the program's CBT strategies [2]; a 90-min protocol training session delivered by PB covering the design and purpose of the study, how to use the training manual, how to embed the digital content in a standard telehealth consultation, and roleplays of case examples; and [3] optional monthly 60-min clinical supervision sessions with PB. Clinicians will have discretion to tailor consultations to participant needs as long as (a) the clinical focus remains burnout; and (b) the program content is delivered in full across the five consultations. Participants will also have independent access to the digital version of Navigating Burnout over the 10 weeks between consultations and be directed by their clinical psychologist to specific components of the program in order to support awareness and management of burnout. During the 10-week treatment period, clinical psychologists providing care in the blended arm will provide immediate risk assessment and intervention for any participant expressing intent to self-harm or suicide and report any concerns related to suicide or self-harm attempts to PB.

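### Optional safety improvement: follow-up surveys are audited 2–3 times per week, so clinician contact starts on average 1.2–1.8 days after a concerning response; an automatic alert for scored flags would shorten this

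*Protocol article*

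**What the plan says.** Section 2.8 (Procedure) of the protocol article sets the detection rule for the post-treatment and 3-month surveys: "Regular safety audits (2–3 times per week) of the post-treatment and 3 months post-treatment surveys will be conducted". Responses that suggest distress or suicidal ideation go to a designated clinical psychologist. Participants who consented to a check-in call are then contacted without delay.

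Both surveys contain the DASS-21 and an open-ended burnout question (section 2.8 and Table 1). The questionnaires are given "alongside open-ended questions about participants" and their experiences of treatment and of burnout. A concern can therefore appear as a score or as free text.

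Three other parts of the article bear on this:

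- **Screening.** Section 2.2 (Participants) excludes people who "report suicidal ideation or problematic alcohol or drug use during screening". Section 2.5 (Recruitment, screening, and consent) rates the two added risk items 0–3, excludes only scores above 1, and has the screening survey "provide links to crisis services and/or TEN where they may find support" for ineligible people where relevant.
- **Treatment period.** Section 2.3 (Interventions) says: "During the 10-week treatment period, clinical psychologists providing care in the blended arm will provide immediate risk assessment and intervention".
- **Contamination.** Section 2.7 (Blinding) says that "references to TEN and Navigating Burnout will be limited in recruitment materials and the PISCF to reduce the risk of contamination".

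**The concern.** Contact is described as immediate, but it can begin only once an audit has found the response. With two or three audits a week, a response can sit unread for days.

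The other safeguards described do not fully cover this period. The treating psychologist's risk assessment applies to one arm of three and to the 10 treatment weeks. At 69 per arm, 2 × 69 = 138 of 207 participants have no treating psychologist in the trial. Screening lowers the risk but does not remove it: a rating of 1 on the ideation item remains eligible. The screen is also at least 10 weeks old at the post-treatment survey and about 10 + 13 = 23 weeks old at the 3-month survey.

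What is at stake is how quickly a distressed participant is reached. Randomisation, the endpoint, the sample size and the treatment estimates are not affected.

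**Working it through.** The article states an audit frequency but no detection delay, so there is no figure of the plan's own to reproduce. The delay follows from the gaps between audits.

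**Inputs**

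- Audits per week: 2 or 3 (section 2.8).
- Audit days and clock time: not stated. Assumed spread over weekdays, at 9.00.
- Submissions: assumed uniform over the 168-hour week.
- Alert reading hours: assumed Monday to Friday, 9.00–17.00. An alert is read at once in those hours, otherwise at 9.00 on the next working day.

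**Formula.** For gaps g between readings that fill the week, the longest wait is max(g) and the mean wait is Σg² / (2 × 168 h).

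**Current rule, spread audits**

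- Monday/Thursday, gaps 72 and 96 h: (5184 + 9216)/336 = 14400/336 = 42.9 h = 1.8 days; longest 96 h (4 days).
- Monday/Wednesday/Friday, gaps 48, 48 and 72 h: (2304 + 2304 + 5184)/336 = 9792/336 = 29.1 h = 1.2 days; longest 72 h (3 days).

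**Sensitivity to spacing** (in days, mean = Σg²/14)

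| Schedule | Gaps | Longest | Mean |
|---|---|---|---|
| Three, exactly equal | 2.33 each | 2.3 | 1.17 |
| Two, exactly equal | 3.5 each | 3.5 | 1.75 |
| Three consecutive weekdays | 1, 1, 5 | 5 | 27/14 = 1.93 |
| Tuesday/Thursday | 2, 5 | 5 | 29/14 = 2.07 |
| Two consecutive weekdays | 1, 6 | 6 | 37/14 = 2.64 |

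Exactly equal gaps would need audits at weekends. The realistic weekday range for the longest wait is 3 to 6 days, and 3 to 4 days is its favourable end.

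**With an alert for scored flags.** The unread periods are four weeknights of 16 h and one weekend of 64 h (Friday 17.00 to Monday 9.00): (4 × 256 + 4096)/336 = 5120/336 = 15.2 h; longest 64 h. The mean falls by 1 − 15.2/29.1 = 48% against three audits and by 1 − 15.2/42.9 = 64% against two. The longest wait falls from 72 or 96 h to 64 h. Free-text disclosures keep the audit wait.

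**With links on the closing screen.** The wait for signposting is zero for every respondent; the wait for a clinician is unchanged. Up to 207 × 2 = 414 surveys would carry the links, or about 414 × 0.70 = 290 if the planned 30% attrition applied at both timepoints.

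The article gives no rate of concerning responses, so neither the number of participants helped nor the number of alerts can be estimated.

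**The case against.** The strongest reply is that a coherent process is already in place. Section 2.8 gives the frequency, the trigger, the escalation and the contact, and immediate contact reads naturally as running from detection. Nothing in the article promises real-time monitoring, and no standard in it is breached by two or three audits a week. This stands: there is no contradiction and no wrong figure. What remains is that a stated rule can be improved cheaply.

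The second reply is that closing-screen text and survey alerts are build details which a condensed article leaves out. A reader might infer that follow-up respondents receive no crisis signposting at all. The article does not say so, and its silence cannot establish it. The links are therefore proposed only if they are not already there. The alert stands on firmer ground, because it improves on an audit frequency that the article does fix.

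A reader might also infer that links would remove the delay. They would not: they speed up signposting, and the wait for a clinician stays the same.

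Nor does the contamination rule require TEN links to be withheld from both surveys. It concerns recruitment materials and the consent form, and section 2.8 itself gives TEN information to the self-guided and control arms after the 3-month survey. That provision is a relevant support route at one of the two timepoints, although it is not crisis signposting and no exact timing is given. The reason for avoiding TEN links holds only at the post-treatment survey, before the primary endpoint is collected.

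Finally, the delay figures rest on assumed audit days and submission times, and they describe the wait for contact only among participants who consented to a call.

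**Conclusion.** The point holds as an optional participant-safety improvement. Under the stated rule, contact with a consenting participant starts on average about 1.2 to 1.8 days after a concerning response, and at most about 3 to 4 days after it when audits are spread over weekdays. Because the article fixes no spacing, clustered weekday audits could stretch the longest wait to 5 or 6 days.

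An alert for scored flags would bring the mean to about 15 h, if it is read in weekday hours, but would leave a weekend maximum of about 64 h. The size of the benefit in participants is unknown.

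This is not evidence of an unsafe or self-contradictory plan, and it has no bearing on the validity of the results.

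**What to change.** 1. **Alert.** Add an automatic REDCap alert to the responsible psychologist when a follow-up survey is submitted with DASS-21 anxiety above 7 or depression above 10 (the screening cut-offs in section 2.5), or with an endorsed risk item if the two added items are kept at follow-up. The existing consent condition for a call would still apply. DASS-21 cut-offs flag distress and not suicidality, so the alert adds to the audit and does not replace it.
2. **Audits.** Keep them for free text and fix spread-out days, such as Monday, Wednesday and Friday.
3. **Links.** Unless the survey build already does so, show crisis-service links on the closing screen of both follow-up surveys to all respondents. This also reaches those who declined a call, for whom section 2.8 describes no contact. Leave out TEN links at the post-treatment survey only.

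The cost is a short amendment, a closing-screen text and one new alert configuration. Crisis links by branching logic are already described for the screening survey; a clinician alert is not. The psychologists would have to triage some false alerts, in a number that the article does not allow to be estimated.

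### The safety audit in section 2.8 leaves out the baseline survey, so distress first written in the baseline free text has no described reader (minor)

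*Protocol article*

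**What the plan says.** The safety monitoring of survey answers is set out in section 2.8 (Procedure) of the protocol article: "Regular safety audits (2–3 times per week) of the post-treatment and 3 months post-treatment surveys will be conducted". Under this audit, "any responses indicative of distress or suicidal ideation will be reported to" a clinical psychologist on the trial team. A call follows on a condition: "If a participant consented to a check-in call related to indicators of distress or suicidal ideation".

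The same section gives the timing of the questionnaires: "The OLBI, DASS-21, WSAS, WHO-HPQ, and TIS-6 will be completed at baseline, post-treatment, and 3 months post-treatment". Table 1 adds the free-text item on burnout at all three times: "Open-ended burnout X X X".

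Before baseline there is screening. Section 2.2 (Participants) excludes people with "DASS-21 symptom scores in the Severe or Extremely Severe ranges for anxiety or depression during screening", and also those who report suicidal ideation or problematic alcohol or drug use. Section 2.5 says that the screening survey asks people to "confirm the inclusion criteria, as well as complete a modified version of the DASS-21 to confirm the absence of exclusion criteria". The two added risk items are scored 0 to 3 and a score above 1 excludes. People who give the higher ratings are emailed by a clinical psychologist.

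During treatment, section 2.3 gives the blended arm psychologists who assess and act on risk. For the self-guided arm (section 2.3) and the control arm (section 2.4), the contact described is fortnightly reminders or emails.

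**The concern.** The audit names two of the three scheduled surveys. The third, baseline, holds the same two instruments in which distress could show, the DASS-21 and the open-ended question. Followed as written, the procedure gives nobody the task of reading baseline answers for risk.

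At stake is a participant's safety, not an estimate. A doctor with burnout may write something worrying in the baseline free text, be randomised to an arm without a therapist, and hear from nobody about it. A similar disclosure in a follow-up survey would fall within the audit.

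**Working it through.** There is no plan figure to reproduce. The check sets the sections side by side and then counts surveys.

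**1. What each survey holds, and who reads it for risk**

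| Survey | DASS-21 | Free text on burnout | Described risk handling |
|---|---|---|---|
| Screening (2.5) | Yes, modified, with two risk items | None described | Exclusion rules, support links, psychologist email |
| Baseline (2.8, Table 1) | Yes | Yes | None described |
| Post-treatment (2.8, Table 1) | Yes | Yes | Audit 2–3 times a week |
| 3 months post-treatment (2.8, Table 1) | Yes | Yes | Audit 2–3 times a week |

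**2. What screening covers.** The exclusion limits are "anxiety (DASS-21 anxiety subscale score >7) or depression (DASS-21 depression subscale score >10", and a score above 1 on either risk item. Someone who passes has already answered the DASS-21 and the two risk items. A second DASS-21 at baseline therefore adds little that is new. The free text is different: screening is described without an open-ended item, so baseline is the first described place where a participant can write about distress in their own words.

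**3. What happens next, by arm.** Blended participants meet a psychologist. If the first consultation is more than three weeks after baseline, they also repeat the OLBI and DASS-21, partly so that clinicians have current data (section 2.8). Nothing comparable is described for the other two arms, where the first audited survey comes after the 10-week treatment period.

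**4. Size.** Inputs: 69 participants per arm and 207 in total (section 2.12); three measurement points (section 2.8).

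- Scheduled surveys outside the audit: 1 of 3 per participant, so 3 × 69 = 207 at full enrolment.
- Of these, from the self-guided and control arms: 2 × 69 = 138, and 138 / 207 = 67%.

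These are counts of surveys, not of people in distress. Baseline is completed before randomisation, so the 67% describes how many participants later have no described clinician contact. It says nothing about the baseline answers themselves.

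**5. Added audit load**

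- Full return: 2 × 207 = 414 surveys now; 414 + 207 = 621; 207 / 414 = +50%.
- If the 30% attrition of section 2.12 applied to both follow-ups: 2 × 0.7 × 207 ≈ 290 now; 290 + 207 = 497; 207 / 290 ≈ +71%.

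**The case against.** The strongest reply is that the design is coherent as it stands: risk is screened at entry and audited afterwards. This largely holds. Screening removes the more severe anxiety and depression and the higher risk-item scores, and it does so before baseline. It is the reason for calling the remaining gap small.

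A second reply is that an article condenses, and the full protocol may already provide for baseline answers. That would count against a complaint about silence. Here, however, the article lists the audited surveys, and the list stops short of one that holds the same instruments. If baseline is already reviewed in practice, the sentence only needs to say so.

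A third reply is that everyone enrolled reports burnout, so some distress in the free text is expected, and section 2.8 sets no threshold for what is reportable. This is fair, but it applies equally to the follow-up surveys, where the trial has accepted the task.

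Some stronger readings are tempting and not supported:

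- *High baseline stress scores go unnoticed.* No exclusion limit is stated for stress, but screening collects those items too, and stressed doctors are expected in a burnout trial. Nothing says that a high stress score alone would be reported at follow-up.
- *Participants may have worsened between screening and baseline.* The interval is not stated, and only a registration check is described between the two. Material worsening is conjecture.
- *Suicidal-ideation scores at baseline go unread.* The two risk items are described for the screening version only. The article does not say that the baseline DASS-21 carries them.
- *A definite number of participants is left at risk.* The article gives no rate of disclosure, so none can be derived.

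**Conclusion.** The point stands as a minor safety matter. Section 2.8 limits the audit to the two follow-up surveys, and no described step reads the baseline survey for risk. After crediting screening, the remaining gap is mainly distress or suicidal ideation first disclosed in the baseline free text. It matters most in the self-guided and control arms, 138 of 207 participants, where no clinician contact is described before the first audited survey.

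This rests on two assumptions: that the sentence in section 2.8 is the full scope of the audit, and that screening has no free-text item, as described. The number of participants who would disclose something reportable is unknown and may be very small. A baseline audit would not detect deterioration during treatment, and it would not reopen a screening ideation score of 1, which the rules allow. Power and the primary analysis are unaffected.

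**What to change.** In section 2.8, extend the audit sentence to name the baseline survey alongside the two follow-up surveys, at the same frequency, with the same reporting route, and applied alike in all three arms. Obtain consent to a check-in call by baseline, either in the consent form or as one item in the baseline survey, because the article does not say where that consent is collected. Do not make it an eligibility criterion, and do not hold up randomisation for it.

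The cost is one changed sentence, possibly one consent item, and about 207 more surveys for the same staff to read. There may also be a few clinician calls near the start of treatment in two arms that otherwise have no person-to-person contact. That is a small departure from the intended contrast between arms. Calls after the post-treatment survey, which the plan already allows, can likewise precede the 3-month endpoint. Recording any such calls by arm would let the report state how many there were. Eligibility rules, randomisation and analysis stay as they are.
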